## 1. ABSTRACT

This proposed R01 is in response to the PAR-21-081 Addressing Health Disparities among Immigrant Populations through Effective Interventions. Chinese immigrants are the second largest immigrant group in the U.S., who suffer disproportionately high type 2 diabetes (T2D) burden and have poor diabetes outcomes. Diabetes Self-Management Education and Support (DSMES) programs are evidence-based interventions that provide patients with important knowledge and skills to navigate diabetes self-management at home. However, numerous social determinants of health (SDOH) barriers limit the access of DSMES programs to Chinese immigrants, including high rates of poverty, limited English proficiency (LEP), and lack of access to care and insurance. Given the high T2D burden and rapid growth in the Chinese immigrant population, there is an urgent need for research to make DSMES accessible to this minority group. High text message use in Chinese immigrants suggests a promising mechanism for enhancing access to DSMES. Yet, this mobile health (mHealth) intervention alone is likely insufficient to address many SDOH barriers reported by LEP Chinese immigrants (e.g., lack of insurance, financial barriers). The community health worker (CHW) model has been shown to be effective for addressing SDOH barriers in health disparity populations. Guided by the NIMHD Research Framework, we argue that a mHealth intervention that is supplemented with CHW support is a novel model for enhancing access to DSMES in Chinese immigrants. Our pilot work demonstrates the feasibility, acceptability, and potential efficacy of a text message-delivered video-based DSMES intervention. The goal of this R01 is to examine the efficacy of the video-based DSMES (hereafter VIDEO) or the video-based DSMES+CHW (hereafter VIDEO+CHW) intervention compared with a wait-list control group (hereafter CONTROL) to improve glycemic control among Chinese immigrants with T2D in NYC. Participants will be randomized with equal allocation to one of the 3 groups. The VIDEO group will receive 1 DSMES brief video/week for 24 weeks delivered via text message. The VIDEO+CHW group will receive same DSMES videos plus bi-weekly support calls from a CHW for 24 weeks. The CHW will assess participants' SDOH barriers to T2D care and link them to available resources in the community. The CONTROL group will continue to receive their usual care and at the end of the study, they will receive DSMES videos. The primary outcome is HbA1c at 6 months. This study will provide critical information on whether it is efficacious to use an existing social media platform or social media plus CHW support to enhance access to DSMES. If either of the interventions is proven efficacious, this project can provide important data for future scaling of this intervention. This study may serve as a program model for chronic care in other high-risk immigrants such as LEP Hispanic immigrants who also bear a high T2D burden, face similar barriers to accessing DSMES programs, and frequently use social media (e.g., WhatsApp).

## 2. PURPOSE OF THE STUDY AND BACKGROUND

### 2.1 Background

Asian Americans are the fastest growing minority group and projected to surpass Hispanic population growth, becoming the largest immigrant group in the US by year 2065. As the largest Asian subgroup, Chinese immigrants bear high type 2 diabetes (T2D) burden, particularly in New York City (NYC) where roughly 1 in every 2 has T2D or prediabetes. Compared to non-Hispanic whites, Chinese immigrants with T2D have higher rates of poverty and limited English proficiency (LEP) and poorer diabetes outcomes. Given the substantial and growing Chinese immigrant population and high T2D burden, there is an urgent need for effective diabetes control interventions in this group.

Diabetes self-management education and support (DSMES) programs are evidence-based interventions that provide patients with important knowledge and skills to manage T2D at home. However, many social determinants of health (SDOH) barriers limit the access of DSMES to Chinese immigrants, including high rates of LEP, poverty, being uninsured, and poor access to

care. Furthermore, there is a significant shortage of cultural- and linguistic-concordant certified diabetes educators to deliver DSMES. These barriers are further amplified by the fact that DSMES is often delivered via multiple in-person visits, which can be challenging for LEP Chinese immigrants who often have long working hours and limited sick time from work.

High text message use in Chinese immigrants suggests a promising mechanism for enhancing access to DSMES. A mobile health (mHealth) intervention that leverages social media may have unprecedented advantages for increasing access to DSMES and holds strong promise for scalability. Yet, mHealth alone cannot address many SDOH barriers to care. The NIMHD Research Framework highlights the importance of addressing multi-level SDOH barriers in health disparity populations. The community health worker (CHW) model has demonstrated efficacy for addressing SDOH barriers and providing critical support to underserved LEP immigrants. We argue that a mHealth intervention that is supplemented with CHW support is a novel model for enhancing access to DSMES in Chinese immigrants. Despite the wide usage of text message in LEP Chinese immigrants, no studies have examined the efficacy of a social media-based DSMES or social media plus CHW model to make DSMES programs more accessible.

In our prior study, we successfully developed 24 culturally and linguistically tailored DSMES videos. Video links were shared via the free and popular social media platform with 30 Chinese immigrants with T2D. The mean video watch rate was high (92%). In our one-arm feasibility pilot, we found HbA1c at 6 months significantly declined by 0.6% compared to baseline (95% CI: 0.3%-0.9%,  $p=0.001$ ). Chinese immigrants also reported they needed assistance with SDOH barriers to T2D (e.g., lack of insurance, financial barriers to accessing medication or glucose testing strips). Building upon these pilot data, the overall goal of **this R01 study** is to examine the efficacy of the video-based DSMES (hereafter VIDEO), or the video-based DSMES+CHW intervention (hereafter VIDEO+CHW) compared with a wait-list control group (hereafter CONTROL) to improve glycemic control among 405 Chinese immigrants with uncontrolled T2D in NYC. Participants will be randomized with equal allocation to one of the 3 groups. The VIDEO group will receive 1 DSMES brief video/week for 24 weeks delivered via text message. The VIDEO+CHW group will receive the same DSMES videos plus bi-weekly support calls from a CHW for 24 weeks. The CHW will assess participants' SDOH barriers to T2D care and link them to available resources in the community. The CONTROL group will continue to receive their usual care and at the end of the study, they will receive DSMES videos. Measurements will occur at baseline, 6, and 12 months.

## 2.2 Aims

**Aim 1:** Examine the efficacy of the VIDEO and VIDEO+CHW interventions on HbA1c (primary outcome) at 6 months

*Hypothesis:* We hypothesize that the VIDEO+CHW group will have the largest reduction in HbA1c, followed by the VIDEO group, and then the CONTROL group at 6 months.

**Aim 2:** Examine the efficacy of the VIDEO and VIDEO+CHW interventions on patient-centered outcomes (secondary outcomes) at 6 months. Secondary outcomes include enhanced self-efficacy, adherence to diabetes self-management behaviors, healthy eating, physical activity and medication taking.

*Hypothesis:* We hypothesize that the VIDEO+CHW group will have the greatest improvements in secondary outcomes, followed by the VIDEO group, and then the CONTROL group at 6 months.

**Aim 3 (exploratory):** To explore the long-term impact of the VIDEO and VIDEO+CHW interventions on HbA1c at 12 months

**Aim 4:** Examine the reach, adoption, fidelity, and maintenance of the VIDEO+CHW intervention within clinical and community settings, and use the implementation frameworks (RE-AIM, CFIR) to delineate contextual factors influencing implementation outcomes (Implementation Evaluation)

### 3. METHODS AND PROCEDURES

#### 3.1 Study

##### Design

The proposed study is a 3-arm RCT of 12 months duration. Participants will be randomized with equal allocation to

| Intervention Components (rows) and Groups (columns)                      | CONTROL | VIDEO | VIDEO+CHW |
|--------------------------------------------------------------------------|---------|-------|-----------|
| Standard of T2D care                                                     | X       | X     | X         |
| 1 DSMES video/week for 24 weeks                                          |         | X     | X         |
| Bi-weekly phone calls from CHWs on addressing SDOH barriers for 24 weeks |         |       | X         |

Table 1. Intervention Components (rows) and Groups (columns)

one of 3 arms (n=135 each): 1) wait-list control (hereafter CONTROL); 2) video-based DSMES intervention (hereafter VIDEO); or 3) video-based DSMES+CHW intervention (hereafter VIDEO+CHW). All of the groups will continue to receive standard of care treatment for their T2D. The VIDEO group will receive 1 brief DSMES video per week for a total of 24 weeks. The VIDEO+CHW group will receive the same DSMES videos plus bi-weekly support calls from a trained CHW for 24 weeks. The CONTROL group will continue to receive their standard of care for T2D during the study duration and at the end of the study, they will be provided the opportunity to receive DSMES videos.

Rationale for a 3-arm RCT: The VIDEO intervention, if efficacious, would be more scalable than the VIDEO+CHW intervention, warranting investigation of the VIDEO intervention alone. However, evidence suggests that health disparity populations, including underserved low-income LEP immigrants, may require additional support to help address community level and SDOH barriers to care (e.g., lack of insurance, financial hardship to cover medication or test strips cost), which the VIDEO intervention alone is unlikely to address. According to the NIMHD Research Framework, patient health outcomes will depend on multiple levels of influence, including individual, interpersonal, community, and societal levels. Within each level, there are 5 domains to consider, ranging from biology, behavior to healthcare system. VIDEO intervention will provide important diabetes education to participants and empower them to become an activated patient on the individual level. In order to reduce health disparities and improve health outcomes, interventions should also consider other levels of influence and address SDOH barriers in LEP Chinese immigrants. Use of CHWs has been shown to be an effective model for addressing SDOH barriers in underserved immigrants. Therefore, we will examine the incremental effect of CHW support on video-based DSMES to understand whether there are any added benefits. A CONTROL group allows us to estimate the effect sizes for each of the intervention components compared to usual care and account for some potential unmeasured confounding variables. Findings from this 3-arm RCT will provide critical data on highly scalable strategies to address access issues of DSMES programs in health disparity populations.

#### 3.2 Sample and Sites

We will recruit 405 Chinese immigrants with uncontrolled T2D, who are currently receiving care at the Charles B. Wang Community Health Center (CBWCHC), a federally qualified health center located in both Manhattan Chinatown and Queens Chinatown. In 2020, CBWCHC provided a total of more than 233,000 service visits to more than 52,000 underserved Asian Americans in Greater NYC. The majority of patients are Chinese, limited English proficient (89%), and have an

income at or below 200% of poverty (84%). CBWCHC was chosen as our main recruitment site for several reasons: 1) there are existing collaborations with this site; [name] has been working with CBWCHC since 2016; 2) [name] is the Section Chief of Internal Medicine at the CBWCHC Queens Chinatown location and has clinical privileges at this site. He has been and will continue to act as a clinical site champion, and provide access to potential participants; and 3) CBWCHC is one of the largest and leading community centers in NYC, having established a trusting relationship with the Chinese American community

CBWCHC will not be engaged in research activities and their role is to identify/refer patients and provide space for this study. All research related activities (e.g. recruitment, consenting, conducting study procedures) will be performed by NYU study staff. The letter of support has been uploaded in the attachment section.

To maximize recruitment efforts, we will also identify potential private practices or community based organizations in Chinatown areas and work with them to recruit potential participants. In addition, we will identify and recruit participants into the study from NYU Langone Health. Similar to the procedures at CBWCHC, all of the research related activities (e.g. recruitment, consenting, conducting study procedures) will be performed by NYU study staff. The role of NYU Langone Health, these private practices or community-based organizations is to help to identify/refer patients and/or provide space for this study.

**Sample Size Estimates: Primary Outcome (HbA1c at 6 months):** The primary aim is to examine the efficacy of the VIDEO and VIDEO+CHW interventions on HbA1c (primary outcome) at 6 months. We hypothesize that the VIDEO+CHW group will have the largest reduction in HbA1c, followed by the VIDEO group and then the CONTROL group at 6 months ( $HbA1c_{VIDEO+CHW} < HbA1c_{VIDEO} < HbA1c_{CONTROL}$ ). Based on our preliminary data, we expect to observe a 0.6% difference between the VIDEO and CONTROL groups. Based on data of a prior CHW intervention in Hispanic immigrants with T2D, we expect to see a group difference of 0.4% between the VIDEO+CHW and VIDEO groups. Using the observed  $SD=0.8\%$  of HbA1c in our preliminary study, based on a two-sample two-sided t-test,  $n=86$  (per group) will be required to detect a minimum group difference of 0.4% in HbA1c with a power of 80% and a type I error of 0.0167 (to account for 3 group comparisons). We will abstract HbA1c data from the electronic medical record, which often has a high rate of missing data due to various reasons (e.g., patients miss the A1c appointment or change to a different health care system). Our pilot study achieved 70% completion rate of A1c follow up data. With a conservative rate of 60-65%, we will recruit 405 (135/group) participants to yield a final sample of at least 258 (86/group). We believe a sample of 405 will provide sufficient power to detect significant differences between the three groups (VIDEO+CHW vs. VIDEO; VIDEO vs. CONTROL; VIDEO+CHW vs. CONTROL).

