| Secondary Outcomes                                                                                                                                                                                                                                                                                                                                                  | • Change in HbA1c at 12 months and changes in self-efficacy,  diabetes self-management behaviors,  dietary intake,  physical activity,  medication adherence,  and SDOH  (at 6 and 12 months) | • Patient data from EHR
• Patient survey
• Healthify referrals                                                                                                                                                                        | • Baseline, 6 months, 12 months                                                                                                                                                               |                                                                   |
| ADOPTION: Did the organization use the program?                                                                                                                                                                                                                                                                                                              |                                                                                                                                                                                                                                                                                                     |                                                                                                                                                                                                                                             |                                                                                                                                                                                               |                                                                   |

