## 7. DATA ANALYSIS AND DATA MONITORING

### 7.1 Data Analysis

**Analytic Plan for Aim 1:** An “intent-to-treat” approach will be used to address the specific aims. For Aim 1, we hypothesize that the VIDEO+CHW group will have the largest reduction in HbA1c at 6 months, followed by the VIDEO group, and then the CONTROL group. A random effects linear mixed modeling will be used to test time-specific differences attributable to the intervention. We also will use the “lincom” command in Stata to estimate differences in time-specific changes from baseline. Randomization should obviate the need for adjustment, but in the case of unbalanced baseline covariates, these will be included as necessary in adjusted analyses. We will use splined linear mixed models with repeated measures to compare changing trends in different periods: 0-6 months and 6-12 months. In this analysis, we will adjust for the covariates as needed.

**Analytic Plan for Aim 2:** For Aim 2, we hypothesize that the VIDEO+CHW group will have the greatest improvements in secondary patient-centered outcomes. Similar to the plan for Aim 1, we will use random effects linear mixed models, adjusting for relevant covariates in the case of unbalanced covariates between the treatment arms at baseline. We will use splined linear mixed models with repeated measures to compare changing trends in different periods, adjusting for the covariates as needed.

**Analytic Plan for Aim 3:** For exploratory Aim 3, we hypothesize that the VIDEO+CHW group will have the largest reduction in HbA1c at 12 months. Similar to the plan for Aim 1, we will use linear mixed effects models and splined linear mixed models with repeated measures to compare changing trends in different periods, adjusting for relevant covariates if needed.

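### The single-step 0.0167 level for the three 6-month HbA1c contrasts is valid but needlessly weak; a step-down test keeps 5% family-wise error and, under the planned effects, adds about 10 points of power for VIDEO+CHW vs VIDEO

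*Protocol*

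**What the plan says.** Protocol section 3.2 (Sample Size Estimates) takes 6-month HbA1c as the primary outcome and names three pairwise contrasts: VIDEO+CHW vs VIDEO, VIDEO vs CONTROL, and VIDEO+CHW vs CONTROL. The calculation is "based on a two-sample two-sided t-test" and arrives at 86 evaluable participants in each arm for a smallest difference of 0.4%. Its error rates are set "with a power of 80% and a type I error of 0.0167 (to account for 3 group comparisons". The SD is 0.8%. On effects, "we expect to observe a 0.6% difference between the VIDEO and CONTROL groups", and a further 0.4% is expected between VIDEO+CHW and VIDEO, so 1.0% is implied between VIDEO+CHW and CONTROL.

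Protocol section 7.1 gives the Aim 1 analysis: "A random effects linear mixed modeling will be used to test time-specific differences attributable to the intervention", with Stata contrasts for changes from baseline and splined models for trends. It states no significance level and no order of testing. The 0.0167 in section 3.2 is the only level in the document.

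**The concern.** Bonferroni holds every contrast to 0.05/3 whatever the other contrasts show. With three arms this gives away power, because the hypotheses are logically linked: if any two pairwise nulls are true, all three means are equal. Once one difference is established, at most one of the other two nulls can still be true, so both can be tested at 0.05 without exceeding 5% overall.

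The contrast that pays is VIDEO+CHW vs VIDEO. It has the smallest expected difference, and section 3.1 gives the incremental effect of CHW support as a reason for having three arms. The other two contrasts have power above 99% under the planned effects, so almost all the power that can be recovered is on this one.

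**Working it through.** **Inputs (Protocol section 3.2).** Difference 0.4%; SD 0.8%; two-sided level 0.0167 = 0.05/3; power 80%; 86 evaluable per group. Expected means relative to CONTROL are 0, −0.6 and −1.0 (0.6 + 0.4). Completion is 60–65% of 135 per group.

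**1. The plan's own figure.**
- Normal approximation: n = 2(z₁₋α/₂ + z₁₋β)²(SD/δ)² = 2 × (2.393 + 0.842)² × (0.8/0.4)² = 83.7, so 84.
- Two-sample t-test (noncentral t): 85.16, so 86. This matches the protocol.

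**2. Power for the 0.4% contrast at each level.** The noncentrality is δ / (SD√(2/n)).
- n = 86: 0.4 / (0.8 × √(2/86)) = 3.279. With the variance pooled over three arms (3 × 85 = 255 df), the critical values are 2.410 at 0.05/3 and 1.969 at 0.05. Power is 80.7% and 90.4%. With two-arm degrees of freedom it is 80.4% and 90.3%.
- n = 81 (135 × 0.60): the noncentrality is 3.182. Power is 77.9% and 88.7%.

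**3. Why a step-down test reaches the 0.05 figure here.** Holm tests the ordered p-values at 0.05/3, 0.05/2 and 0.05. Shaffer's three-arm version uses 0.05/3, then 0.05 for both of the others. At 86 per group, the 1.0% contrast has power of essentially 100% even at 0.05/3, and the 0.6% contrast has 99.4% at 0.05/3 and 99.6% at 0.025. The 0.4% contrast is therefore nearly always tested at 0.05.

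**4. Simulation** (200,000 trials per scenario, 86 per group, SD 0.8, pooled-variance t-tests). Entries are power in %.

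| True means (CONTROL, VIDEO, VIDEO+CHW) | Quantity | Bonferroni | Holm | Shaffer | Global F at 0.05, then pairs at 0.05 |
|---|---|---|---|---|---|
| 0, −0.6, −1.0 | VIDEO+CHW vs VIDEO | 80.8 | 90.5 | 90.5 | 90.5 |
| 0, −0.6, −1.0 | all three contrasts | 80.2 | 90.3 | 90.3 | 90.3 |
| 0, −0.4, −0.8 | all three contrasts | 62.1 | 80.7 | 80.8 | 80.8 |
| 0, 0, −0.4 | VIDEO+CHW vs VIDEO | 80.7 | 83.5 | 86.9 | 88.3 |
| 0, −0.2, −0.4 | VIDEO+CHW vs CONTROL | 80.8 | 81.4 | 82.1 | 83.4 |

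The first row agrees with step 2 to within simulation error. At 81 per group and the planned means, the simulated values are 78.0% for Bonferroni and 88.7% for each of the other three.

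**5. Family-wise error in the same simulations.** Under the global null it was 4.5% for Bonferroni, Holm and Shaffer and 5.05% for the F-gated test (5% within simulation error). With one true null pair, Holm, Shaffer and the F-gated test were all at or below 5.03%.

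**6. Is each alternative at least as powerful as Bonferroni?** Holm and Shaffer reject everything Bonferroni rejects, by construction. The F-gated test does not quite. If the middle mean lies exactly midway, F = t²/2 for the extreme pair, so the gate needs |t| > √(2 × 3.031) = 2.462 (p < 0.0145), against 2.410 for Bonferroni.

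**The case against.** The strongest reply is that nothing is broken. Bonferroni is valid, the sample size is correctly computed, and at 86 per group the trial reaches its 80% target at the level it states. That stands: this is a point about efficiency, not a sample-size error.

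Bonferroni also brings simultaneous confidence intervals, and section 3.1 says the control group is there to estimate effect sizes. That stands too, and it is a real price of the change.

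The gain of about 10 points belongs to the planned effects and shrinks under others, as the table shows. All figures use a t-test approximation, whereas section 7.1 plans a mixed model, so they illustrate the gain and are not this trial's exact power.

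Two stronger readings are tempting, and the document supports neither:
- **Unadjusted testing.** Because section 7.1 gives no level, a reader might infer that each contrast will be tested at 0.05, which would give a family-wise error of about 12% under the global null. No section proposes this, the only stated level is 0.0167, and the testing rule may be in a statistical analysis plan that is not shown.
- **A contradictory confirmatory family.** Aim 3 is labelled exploratory, "To explore the long-term impact of the VIDEO and VIDEO+CHW interventions on HbA1c at 12 months", while Table 2 lists "Change in HbA1c at 12 months and changes in self-efficacy" under secondary outcomes. The labels do differ. Section 3.2, however, ties 0.0167 to HbA1c at 6 months, and neither label brings the 12-month value into that family.

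**Conclusion.** The point holds as a better method for the same error rate. Single-step Bonferroni is acceptable but weaker than it needs to be for three arms. Under the protocol's expected means and SD, a step-down test raises power for VIDEO+CHW vs VIDEO by about 10 points at 86 per group, and by about 11 points at 81 per group, where Bonferroni falls below 80%. With less favourable effects the gain is modest: 3 points (Holm) to 8 points (F-gated) if only one arm differs, by 0.4%, and about 1 to 3 points for the largest contrast when the arms are evenly spaced 0.2% apart. These figures assume a common SD of 0.8%, equal evaluable numbers per arm, normal-theory tests and a family of exactly three 6-month contrasts. Shaffer's step and the F-gated argument, as used here, are specific to three arms.

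**What to change.** In section 7.1, state that the three pairwise 6-month HbA1c contrasts form the confirmatory family and are tested at a two-sided family-wise level of 0.05 by one named procedure:
- **Preferred:** Holm, or Shaffer's three-arm version (smallest p-value at 0.0167; if significant, the other two each at 0.05). Neither can do worse than Bonferroni.
- **Acceptable alternative:** a global 2-df test of arm at 6 months at 0.05 and, if significant, each pair at 0.05.

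Keep 0.0167 in section 3.2 as the conservative sizing basis, and add the step-down power with its assumptions and at least one less favourable scenario. If simultaneous coverage is wanted, report Bonferroni-adjusted intervals beside the unadjusted 95% intervals, and note that the adjusted intervals may not always agree with the step-down decisions.

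The cost is wording only, with no change to recruitment, data collection or the model. The change should be fixed before anyone sees outcome data by arm. If a statistical analysis plan exists, it should carry the same rule.

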##### **4.4.2 Intervention Arms**

**Wait-list control group (CONTROL):** Participants in this group will continue to receive the standard of usual care for their T2D at their doctor's office during the course of our study. At the end of the study, the CONTROL group will be provided the opportunity to receive DSMES videos.

**Video-based DSMES (VIDEO):** Participants in the VIDEO group will receive brief pre-recorded DSMES videos, which include both educational and SCT-based behavioral content. All intervention videos have been linguistically and culturally tailored and pilot tested in a prior study. Similar to the prior study, we will deliver video links via text messages. We will send 1 DSMES video each week for a total of 24 weeks with each video lasting about 5 minutes in duration. Our preliminary data demonstrated high feasibility and acceptability of these DSMES videos.

**Video-based DSMES+CHW (VIDEO+CHW):** Participants in this group will receive the same DSMES videos as described above. In addition, they will also receive brief phone calls from CHWs every 2 weeks during the 24 weeks video program. During these calls, CHWs will assess whether participants need assistance on SDOH barriers (e.g., health insurance enrollment, financial assistance on covering medication/test strips, food assistance). If needed, CHWs will link participants to available services within the community. CHWs will also provide assistance on navigating the complex health care systems and serve as an advocate for patients during doctor visits if needed. These phone calls will be audio recorded for data integrity and quality assurance. We will randomly select phone call audio recordings to ensure that they are following our study protocol. Audio recordings will be password protected and stored on the NYU Langone shared drive which is only accessible to our study team members. We will destroy the recordings in July 2029, one year after our grant ends.

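### Covariates for the main Aim 1 model are chosen by observed baseline imbalance, although the protocol plans for up to 35-40% missing record HbA1c for reasons that CHW support may change in one arm only

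*Protocol*

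**What the plan says.** Protocol Section 3.2 (Sample Size Estimates) plans to take HbA1c from the medical record and warns of a high rate of missing values for various reasons. The two examples are that "patients miss the A1c appointment or change to a different health care system". After citing 70% completion in the pilot, it continues: "With a conservative rate of 60-65%, we will recruit 405 (135/group) participants to yield a final sample of at least 258 (86/group").

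Section 4.4.2 gives the VIDEO+CHW arm, and no other, help with insurance enrolment and costs. It adds: "CHWs will also provide assistance on navigating the complex health care systems and serve as an advocate for patients during doctor visits if needed". Section 3.1 says that the videos alone are unlikely to address such barriers.

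Section 7.1 promises intent-to-treat and a random effects linear mixed model for Aim 1. It expects randomisation to make adjustment unnecessary, but "in the case of unbalanced baseline covariates, these will be included as necessary in adjusted analyses". For the splined models it allows adjustment as needed. Section 4.5 says the same of acculturation, and no criterion is given in either place.

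Section 4.5 also lists a social determinants of health (SDOH) survey and the diabetes medication regimen among the covariates collected. It adds the staff-guided A1CNow test because of gaps in the record, and Section 4.6 pays for that test at baseline, 6 and 12 months. Table 2 (Section 4.7) still names only the electronic record as the source of the primary outcome.

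**The concern.** Randomisation balances access barriers among everyone randomised. It does not balance them among those whose 6-month HbA1c is observed. A likelihood-based mixed model handles missing values properly when missingness depends only on what the model contains: arm, time and observed HbA1c. If it also depends on insurance or access, and these predict 6-month HbA1c beyond the baseline value, they need to be in the model.

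A rule triggered by baseline imbalance asks a different question. Because randomisation tends to balance these variables, the rule tends to leave them out, however strongly they predict missingness and outcome.

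At stake are VIDEO+CHW vs VIDEO, which carries the incremental effect of CHW support, and VIDEO+CHW vs CONTROL. VIDEO vs CONTROL is not touched by this mechanism, since neither arm has CHW support.

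**Working it through.** **The plan's own figures.** Inputs from Section 3.2: "based on a two-sample two-sided t-test", to "detect a minimum group difference of 0.4% in HbA1c", SD 0.8, "with a power of 80% and a type I error of 0.0167".

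- The normal approximation gives 84 per group. The noncentral t gives 86 (power 80.4%), so the stated 86 reproduces.
- Missing share: 1 − 0.65 = 35% to 1 − 0.60 = 40%, that is 0.35 × 135 ≈ 47 to 0.40 × 135 = 54 per arm.
- Evaluable per group: 135 × 0.65 = 87.75, but 135 × 0.60 = 81 (power 77.6%). Reaching 86 needs 86/135 = 63.7%. The lower end of the stated range therefore does not deliver the stated 86.
- At the pilot's 70%, 135 × 0.70 = 94.5 per group (power about 84%).

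**Size of a possible bias.** None of the following inputs is in the documents:

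- half of participants have an access barrier;
- with it, 6-month HbA1c is 0.5 points higher given baseline;
- the true difference is −0.40, with or without the barrier;
- missingness (no barrier/barrier) is 20%/60% in VIDEO and 20%/30% in VIDEO+CHW, so 40% and 25% overall.

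Shift in an arm's mean = gap × [P(barrier | observed) − P(barrier)].

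- VIDEO: P(barrier | observed) = 0.5 × 0.40 / 0.60 = 0.333. Shift = 0.5 × (0.333 − 0.5) = −0.083.
- VIDEO+CHW: 0.5 × 0.70 / 0.75 = 0.467. Shift = 0.5 × (0.467 − 0.5) = −0.017.
- Bias in the contrast: −0.017 − (−0.083) = +0.067, so the estimate is about −0.33.

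Variations:

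| Scenario | Bias without the barrier in the model |
|---|---|
| As above | 0.067 |
| Gap 0.3 instead of 0.5 | 0.3 × (0.467 − 0.333) = 0.04 |
| All missingness halved (10%/30% and 10%/15%) | 0.5 × (0.425/0.875 − 0.35/0.80) = 0.024 |
| Same missingness rule in both arms | 0 |

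Simulated trials of 135 per arm, using baseline-adjusted regression on observed 6-month values, agree. Without the barrier the estimate is about −0.33, or −0.38 with missingness halved. With it the estimate is about −0.40 in both.

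Power at 0.0167 is about 71-79% without the barrier and 90-95% with it, depending on how the SD of 0.8 is split between explained and residual variation. With equal missingness there is no bias, and power is about 84-89% without and 89-92% with. That smaller gain is precision alone.

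**Closer to the planned model.** A likelihood model over baseline, 6 and 12 months gives −0.344 to −0.353 in the main scenario, a bias of about 0.05. This assumes the same missingness rule at 12 months and a 6-to-12-month correlation of 0.5 to 0.8. If the device recovers half the missing values at both visits, it gives −0.381 to −0.388, a bias of 0.01 to 0.02.

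**Wider assumptions.** With barrier prevalence 30-50%, gap 0.3-0.8, 60% completion in VIDEO, and no dependence on the barrier at all in VIDEO+CHW, the bias runs from 0.015 to 0.13. The top of that range needs every input at its most extreme.

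**The case against.** The strongest reply is the home test. It needs no clinic visit, staff guide it, participants are paid for it, and it was added because of gaps in the record. It can bypass both example reasons. A reader might infer that 35-40% of participants will end without a 6-month HbA1c. The documents do not support that: the figure is called conservative, lies below the pilot's 70%, and concerns record abstraction. It stands only as the planning figure, not revised for the device.

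A reader might also infer that the protocol bars other covariates, or says that missingness will differ by arm. It does neither. Adjustment as needed is allowed elsewhere, and the two reasons are examples that the protocol does not tie to insurance or SDOH. A differential effect is an inference from what CHWs do. What remains is that the stated rule for the main Aim 1 model is imbalance, and the looser wording sets no criterion.

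A third tempting reading is that the benefit could be overstated by almost half of 0.4. Assuming 37.5% missing in the intervention arm alone, with those values 0.5 points worse than the model predicts, gives 0.5 × 0.375 = 0.19. That is a separate missing-not-at-random scenario. It runs against the idea that CHW support reduces missingness, and covariate adjustment would not cure it. It is not part of this point.

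Sensitivity analyses for missing data and completion by arm may sit in a statistical analysis plan that is not shown, so their absence is not counted.

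**Conclusion.** The point holds in a limited form. The protocol states a covariate rule that does not suit a trial planning for this much missing record data, with an intervention that may act on its causes in one arm. Bias in the VIDEO+CHW contrasts is possible, not shown. Under the illustrative assumptions it is roughly 0.02 to 0.07 points against 0.4, at the lower end or a little below if the device recovers much of the missing data, and near 0 if missingness works alike in all arms. In these scenarios it runs against VIDEO+CHW, so it would hide benefit rather than create it.

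The loss of precision does not depend on differential missingness, only on the covariates predicting HbA1c. Size and sign rest on barrier prevalence, gap and missingness rates that the documents do not give.

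**What to change.** 1. In Section 7.1, replace the imbalance rule for the primary model with a short, fixed list of baseline covariates, included whatever their balance: the insurance and access items of the SDOH survey, recruitment source, and diabetes medication regimen. Use baseline values only, since CHW support may change later ones. If baseline HbA1c is modelled as an outcome, let these covariates have visit-specific effects, so that they can account for 6-month differences given baseline.
2. In Section 3.2, update the completion assumption for the A1CNow device, and state that 86 per group needs at least 63.7% completion.
3. In Table 2, name the device beside the electronic record as a source of the primary outcome.

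The cost is protocol wording and a few model degrees of freedom. The survey and regimen are already collected and the recruitment source is known at enrolment, so no new data or participants are needed.
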